## Abstract

**Introduction:**

Breastfeeding (BF) is the healthiest form of nutrition for babies and is recommended exclusively (EBF) for at least the first six months of life. The carbon footprint of formula feeding (FF) has been studied, but that of BF is unknown.

**Aim:**

To identify the environmental impact of three types of infant feeding taking into account the accessories needed and the diet of postpartum women in the baby’s first month of life.

**Methods:**

This is a multicentre, cross-sectional study conducted in the Barcelona North Metropolitan Area (Catalonia, Spain). The participating sites are primary care settings that will recruit 408 postpartum women (4–6 weeks) as per inclusion/exclusion criteria. The data will be collected through a GREEN MOTHER Survey that includes 4 dimensions: 1) socio-demographic and clinical data; 2) data on the newborn and accessories used in infant feeding; 3) general data on the mother's diet (food consumption habits), and 4) recording of 24 h of the mother’s diet. The data analysis will be performed to check the prevalence of infant feeding types at birth and month 1, as well as a comparative analysis of three types of infant feeding on environmental impact (climate change; water consumption, and scarcity).

Ethics.

This project was approved by the Research Ethics Committee of the Jordi Gol i Gurina University Institute Foundation for Primary Health Care Research (IDIAP) under code 22/101-P dated 22/02/2023.

**Discussion:**

A second phase of the GREEN MOTHER study is planned, which will consist of an educational intervention to promote breastfeeding, nutrition and sustainability. This intervention will be based on the results obtained in Phase I. We expect that the project results – through the publication and dissemination of scientific papers and reports among relevant stakeholders (association of community midwives, healthcare and primary care attention professionals and the public) – will increase public awareness of breastfeeding and its impact on sustainability.

**Trial registration:**

Both phases of the GREEN MOTHER study protocol were registered in ClinicalTrials.gov, NCT05729581.

**Supplementary Information:**

The online version contains supplementary material available at 10.1186/s12937-024-01000-9.

## Background

Breastfeeding (BF) is an eco-friendly, sustainable, and non-polluting form of feeding compared to formula feeding (FF) (for definitions of infant feeding types, see Annex I). It results in less waste production, minimal greenhouse gas (GHG) emissions, a smaller carbon footprint (see definitions of the environmental impacts referred to in this article in Annex I), and smaller water footprint (WF) [1, 2]. According to the Convention on the Rights of the Child [3], all infants and children have the right to the enjoyment of the highest attainable standard of health. The World Health Organization (WHO) recommends that BF be exclusively used for the first six months of life and that it be continued up to two years of age or for as long as the mother and child wish. BF offers multiple physical and mental health benefits for both mother and child and is environmentally friendly [2–4].

Some of the short-term benefits to children’s health include reduction of neonatal mortality, protection against gastrointestinal and respiratory infections, dental malocclusion and atopy [5–7]. In the long term, children and teenagers who were breastfed are less likely to be overweight or obese, are more likely to have healthier cognitive development and score better on intelligence tests, are associated with a higher income as adults, and are less likely to suffer diabetes or cardiovascular disease throughout their lives [4, 6]. Longer exclusive breastfeeding (EBF) also contributes to the health and well-being of mothers [4, 5]. It reduces the risk of ovarian and breast cancer, helps space out pregnancies, and decreases the risk of type 2 diabetes [4–6]. Improved child development and reduced healthcare costs thanks to BF result in financial savings for families, the nation, and society in general [2].

Under the Paris Agreement, the European Commission has set ambitious goals to reduce the continent’s carbon footprint, including a 55% reduction in GHG emissions by 2030 and climate neutrality by 2050 [8].

The manufacture and distribution of industrial infant formula is harmful to the environment, generates polluting waste, and requires energy use to manufacture the formula and packaging materials, and to transport the products, and water use to prepare bottles on a daily basis. Most infant formulas are based on cow's milk. Dairy farms represent the main source of anthropogenic methane emissions. In Europe, livestock farming represents 12–17% (630–863 Mt CO_2_-eq) of total GHG emissions [8].

For an accurate calculation of the environmental impact of breastfeeding, the infant feeding accessories (breast milk pump; milk storage containers or bags, bottles, bottle warmer, and bottle sterilizer, for example) and a theoretical increase of 500 kcal in the diet of the mother must be taken into account [1, 9–12].

There is data on the carbon footprint and water footprint of FF, but there is none on the environmental impact of breastfeeding. The average carbon footprint of FF was estimated to be 9.2, 7, 8.4, and 11 kg CO_2_-eq per kg of formula in New Zealand, USA, Brazil, and France, respectively. The potential carbon savings of BF compared to FF for the UK, China, Brazil and Vietnam is 40–55% [1].

The additional volume of water that a mother consumes while breastfeeding is minor compared to the significant quantities needed for manufacturing formula milk [12]. Research conducted by Pope et al. in the United States demonstrated that producing 1 kg of commercial formula requires 6.6 kg of raw milk, which entails a water footprint (WF) comprising 626 L of blue water for manufacturing, reconstitution, and sterilization, 6,280 L of green water for cow feed, and 524 L of grey water [13]. In Switzerland, Rollins and colleagues estimated that the average WF for whole cow's milk is around 940 L of water per kg of raw milk. When considering that 1 kg of whole milk produces about 200 g of milk powder, the water consumption (WC) amounts to 4,700 L of water per 1 kg of milk powder [14, 15].

Globally, water scarcity presents a significant challenge in fulfilling the need for freshwater for drinking and agricultural purposes [16]. In Spain, food consumption is associated with a water wastage of 3,302 L per person per day. The most substantial environmental impact from water use is attributed to the production of meat, fish, and animal fats (26%), as well as dairy products (21%) [17]. The water footprint of food waste was estimated to be 2,095 hm^3^, equivalent to 131 L per person per day [17]. Given the heightened water stress, this study also assesses the water stress implications of the life cycle of formula production, infant feeding accessories, and maternal dietary practices. There is currently no rigorous data on the GHG savings that Europe could achieve by taking into account the dietary habits of postpartum mothers if BF was their top choice rather than FF. To meticulously compare the contribution of EBF and FF to global warming in terms of their carbon footprint, the various dietary patterns of postpartum women and the accessories required for breastfeeding must be considered. Although there is no consensus on the need to supplement the diet of lactating mothers, it is recommended that they increase their daily calorie intake by 500 kcal to cover the nutritional and energy requirements of feeding their baby [18, 19]. Additionally, to promote public health, the Catalan government issued specific nutritional guidelines for pregnant women [20].

Currently, 92% of mothers want to breastfeed their babies but only 17% do EBF for six months [21]. Stopping BF is most often not the mother’s wish and happens earlier than desired. The most frequent causes of stopping breastfeeding are social barriers [22]. Mothers and families need support to ensure that their children receive optimal BF during the first six months of life, as well as the progressive and appropriate introduction of complementary feeding. Healthcare professionals play an essential role in providing this support [23].

The WHO recommends the support of health services in providing advice on infant and child nutrition. It is committed to supporting countries in accordance with the Global Nutrition Targets approved by Member States [24]. One of these targets is to increase the rate of EBF during the first six months of life to at least 50% [24].

In the 2019 document *Green Feeding Europe*, the Council of the European Union makes a collaborative effort with institutions to inform and involve the Green Parties of Europe, so they include the nutrition of infants and young children in their environmental programmes [12].

In the face of the climate emergency, it is crucial to understand the impact of maternal diet on health and the environment. A change towards a healthier and more environmentally friendly diet should be promoted, while increasing the rates of exclusive breastfeeding can be considered an issue related to public health, social rights, and inequality. Government investment and changes in these areas must be achieved, including longer maternity leave, spaces where women can breastfeed freely and comfortably, the monitoring of surrogate advertising, more promotion of breastfeeding and access to professionals.

To our knowledge, there are no studies on the environmental benefits of breastfeeding, or the quality and type of diet followed by postpartum women in Catalonia, Spain. Therefore, measuring the environmental benefit of breastfeeding may help protect the environment and consequently the health of the population and the planet [25, 26].

This project is split into two independent sequential projects. The results from Phase I will bolster the development of educational materials to be used in Phase II (educational intervention to improve prevalence of breastfeeding and a sustainable diet).

### Hypothesis

EBF will have smaller environmental impact than FF or mixed feeding (MF).

### General Aim

Calculate and compare the environmental impacts (climate change, water consumption and water scarcity) of three infant feeding types (EBF, FF, and MF).

#### Objectives of the study

Primary objective

Determine the environmental impacts (climate change, water consumption and water scarcity) of EBF, MF and FF of postpartum mothers in their baby’s first month of life, taking into account the accessories used for infant feeding and mother´s diet and food consumption habits.

Secondary objectives:

To calculate the prevalence of EBF, FF and MF after birth, and at 4–6 weeks postpartum.To describe the maternal diet in terms of macro, micronutrients and energy consumed.To compare the calories consumed by according to the type of breastfeeding, lactating mothers (EBF and MF) and non-lactating mothers (FF).To compare feeding types with socio-demographic and clinical data.To compare maternal diet and food consumption habits with feeding type and socio-demographic data.

## Methods and analysis

For this article, we used the SPIRIT reporting style for the protocol studies [27].

### Study design

This is a multicentre, cross-sectional study conducted in the Barcelona North Metropolitan Area (Catalonia, Spain) of the Catalan Health Institute (ICS), which provides universal coverage. The participating sites are the primary care settings of Sabadell, Granollers, Santa Coloma de Gramanet, Mollet, Mataró, Badalona, and Sant Adrià.

### Sample size calculation

For the calculation we took into account both the local data on prevalence of three infant feeding types at month 1 [21] and the data provided by the literature for the footprint for consumption of 1 kg powdered breastmilk substitute for the nearest geographical area. This is 11 kg CO2 equivalents and standard deviation 1 in UK/France [1]. Accepting an alpha risk of 5% and a power of 80%, in a two-tailed test, a minimum of 60 subjects are necessary in the EBF group, 60 in the mixed and in 30 in the FF group to recognize as statistically significant a difference greater than or equal to 0.7 units (One-Way ANOVA menu, StudySize 2.0) [28]. The common standard deviation is assumed to be 1 [1] (One-Way ANOVA menu, StudySize 2.0, [28]).

These 150 women (60 + 60 + 30) are the minimum number we need to recruit. However, at the time of recruitment, we do not know which breastfeeding arm each of the participating women will be in during the follow-up month. From our own previous studies [21], we know that after one month of follow-up, from an initial recruitment of 400 women, some 256 (64%) could be breastfeeding exclusively, 92 (23%) using mixed and 52 (13%) a formula feeding [21]. These expected female counts exceed the required minimums in each arm, and would allow replacement rates for losses during follow-up of up to 35%.

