### Procedure

In order to calculate the environmental impacts of the different types of infant feeding, the necessary variables are first to be collected in different questionnaires. Subsequently, the impacts of the types of breastfeeding will be calculated by adding together the impacts associated with the use of accessories, artificial milk and the mothers' diet for each type of infant feeding. The questionnaires are completed by the midwife during the visit with the mother.

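### The 80% power for 0.7 units rests on the spread of a footprint per kg of formula powder, so it is unsupported for the primary comparison of summed impacts

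*Protocol article*

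**What the plan says.** The Sample size calculation section starts from two sources: local prevalence of the three feeding types, and the literature "footprint for consumption of 1 kg powdered breastmilk substitute for the nearest geographical area". It reports the latter as "This is 11 kg CO2 equivalents and standard deviation 1 in UK/France". The test settings are "Accepting an alpha risk of 5% and a power of 80%, in a two-tailed test", the target is a "difference greater than or equal to 0.7 units", and "The common standard deviation is assumed to be 1", with the same literature citation. From these it concludes that "a minimum of 60 subjects are necessary in the EBF group, 60 in the mixed and in 30 in the FF group". It calls the resulting 150 women the minimum to recruit. From 400 recruited it expects 256 EBF, 92 MF and 52 FF, and says this leaves room for losses of up to 35%.

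The Background shows what kind of number 11 is. The average footprint of formula "was estimated to be 9.2, 7, 8.4, and 11 kg" CO2-eq per kg of formula in New Zealand, the USA, Brazil and France respectively.

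The outcome is defined elsewhere. The primary objective covers climate change, water consumption and water scarcity of each feeding type in the first month, taking accessories and maternal diet into account. Under Procedure, the impacts are "calculated by adding together the impacts associated with the use of accessories, artificial milk" and the mothers' diet. Under Dependent variables, climate change is measured in kg CO2eq, not per kg of powder.

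**The concern.** The inputs describe a product and the outcome describes women. A footprint per kg of powder is a property of the formula and its supply chain. The primary outcome varies with how much formula each baby takes, which accessories are used and what the mother ate on the recalled day. An SD for the first says nothing about the spread of the second. For exclusively breastfeeding women, expected to be 64% of the sample, a footprint per kg of powder consumed is not defined at all. The 0.7 has no unit beyond the one it inherits from the powder figure.

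This is the only power statement in the protocol, and the 150-woman minimum and the 35% loss allowance both follow from it. A reader of the results could take a non-significant difference as evidence against a gap of 0.7 kg CO2eq, when the protocol gives no ground for that.

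**Working it through.** **Inputs from the protocol.** Two-tailed alpha 0.05, power 80%, one-way ANOVA, SD 1, difference 0.7; n = 60/60/30 (EBF/MF/FF) as the minimum; 256/92/52 expected from 400. A 35% loss gives 256 × 0.65 = 166.4, 92 × 0.65 = 59.8 and 52 × 0.65 = 33.8, taken as 166/60/34.

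**Step 1: reproduce the stated figure.** Omnibus F test with noncentrality λ = Σ nᵢ(μᵢ − μ̄)² / SD², on 2 and N − 3 df.
- MF midway, means 0 / 0.35 / 0.7: μ̄ = (60 × 0.35 + 30 × 0.7) / 150 = 0.28. λ = 60 × 0.0784 + 60 × 0.0049 + 30 × 0.1764 = 10.29. Power is 81.9%.
- Least favourable MF mean (the weighted mean of the other two, 0.7 × 30/90 = 0.233): λ = (60 × 30/90) × 0.49 = 9.8. Power is 79.9%.

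So 60/60/30 follows from the stated inputs.

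**Step 2: compare the scales.**

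| | Sample size section | Primary outcome |
|---|---|---|
| Unit of observation | 1 kg of formula powder | a woman and her baby |
| Unit of measure | kg CO2e per kg of powder | kg CO2eq |
| Content | formula only | accessories + formula + maternal diet |
| Defined for EBF | no | yes |
| SD given | 1 | none |
| Target difference given | 0.7 | none |

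**Step 3: what survives.** λ depends only on the difference divided by the SD, so the group sizes can be stated in SD units of the per-woman total. For range R in SD units, λ = kR². With MF midway, k = 21.0, 33.2 and 51.0 for the three sets of counts. At the least favourable MF mean, k = n(EBF) × n(FF) / [n(EBF) + n(FF)] = 20.0, 28.2 and 43.2. The λ needed for 80% power is 9.83, 9.75 and 9.71.

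| n (EBF/MF/FF) | R, MF midway | R, least favourable MF |
|---|---|---|
| 60/60/30 | 0.68 SD | 0.70 SD |
| 166/60/34 | 0.54 SD | 0.59 SD |
| 256/92/52 | 0.44 SD | 0.47 SD |

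**Step 4: can the true power be placed above or below 80%?** Only with assumptions. The woman-level SDs below (kg CO2eq per day) are assumed. The differences 0.9 and 1.3 come from an assumed 600–900 ml of formula per day at 0.13 kg powder per litre, that is 0.08–0.12 kg powder, times 11. Omnibus power (%), MF midway:

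| Assumed SD | n | diff 0.7 | diff 0.9 | diff 1.3 |
|---|---|---|---|---|
| 1.5 | 60/60/30 | 45.9 | 68.2 | 95.0 |
| 2 | 60/60/30 | 27.5 | 43.1 | 75.5 |
| 3 | 60/60/30 | 14.3 | 21.1 | 40.3 |
| 1.5 | 256/92/52 | 85.3 | 97.6 | >99.9 |
| 2 | 256/92/52 | 59.9 | 82.5 | 99.0 |
| 3 | 256/92/52 | 29.8 | 46.5 | 79.4 |

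At SD 2 with the expected counts, power runs from 59.9% to 99.0% according to the difference alone. The protocol fixes neither the SD nor the difference, so the table shows the width of the uncertainty and is not an estimate of this study's power.

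**The case against.** The best defence is that ANOVA power depends only on the ratio of difference to SD. Read as a standardised effect of 0.7, the calculation is valid for any outcome, including the summed impact. This stands for the group sizes, and the fix uses it. It does not rescue the text as written, because the section does not call 0.7 standardised: it takes SD 1 from the source of the 11 kg figure and presents both as a footprint.

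A second defence is that the analysis plan presents feeding type with accessories separately from maternal diet, so diet variation would not affect the first heading. That narrows the problem. However, Procedure still defines a summed total, and even without diet the outcome is not a footprint per kg of powder.

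A third is that 150 is a minimum and the plan is for 400 or more. That is correct, and no section sets a stop at 150.

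A reader might also infer that the SD of 1 contradicts the Background, since the four national averages there have an SD of 1.67. It does not: the section cites SD 1 for UK/France, which is a different quantity from the spread of averages over four countries.

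**Conclusion.** Wrong as written. The stated 80% power for 0.7 units is unsupported for the primary comparison, because both inputs sit on the scale of a product footprint. This follows from the protocol's own definitions and needs no outside figure. The arithmetic is correct, and the group sizes stand as a standardised calculation: a range of about 0.7 SD at 60/60/30, and 0.44 to 0.47 SD at the expected counts, depending on where the MF mean lies. These ranges assume equal SDs and the omnibus test.

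A reader might go further and conclude that the study is underpowered, that one-day diet variation will dominate the total, or that 150 women must be declared inadequate. The protocol supports none of these. It gives no woman-level SD and no target difference on the total. Low power appears if 0.7 is held fixed while an assumed larger SD is brought in, but 0.7 is itself off the outcome's scale. A larger true difference reverses the result.

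**What to change.** In the Sample size calculation section:

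1. Remove the justification by the footprint of 1 kg of powder.
2. State the calculation in SD units of the per-woman total impact: with the omnibus ANOVA, 80% power for a range of about 0.7 SD at 60/60/30, 0.54 SD at 166/60/34 and 0.44 SD at 256/92/52 with MF midway. Add that the last two become about 0.59 and 0.47 SD at the least favourable MF mean.
3. Convert to kg CO2eq only for a defined period, and only with a woman-level SD that includes the one-day diet component, either sourced or pooled from the study's own women. Until then, do not describe 150 women as giving 80% power for 0.7 kg CO2e.

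The cost is one reworded paragraph and the loss of a detectable difference in kg CO2e until an SD is sourced. Recruitment, data collection and analysis do not change.

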### Participants, inclusion and exclusion criteria

The study population consists of pregnant women (in their last month of pregnancy) from the previously mentioned primary care centres in the Barcelona North Metropolitan Area of the ICS.

The* inclusion criteria* consist of women assigned to the aforementioned centres, who are at least 16 years old, and are at one of their last pregnancy check-ups (or first postpartum visit).

The* exclusion criteria* are language barriers preventing informed consent and consent withdrawal.

### Recruitment

Midwives from the participating centres recruit women at one of their last pregnancy check-ups (or first postpartum visit) during November 2022 and May 2023. Those who meet the inclusion criteria and agree to participate in the study should be informed about the project and asked to sign the informed consent.

### Procedure

In order to calculate the environmental impacts of the different types of infant feeding, the necessary variables are first to be collected in different questionnaires. Subsequently, the impacts of the types of breastfeeding will be calculated by adding together the impacts associated with the use of accessories, artificial milk and the mothers' diet for each type of infant feeding. The questionnaires are completed by the midwife during the visit with the mother.

#### Data collection

Three questionnaires are to be prepared, using the REDCap platform [29]:Recruitment visit (indicating the moment in which they are recruited, visit week 38–40): Questionnaire concerning the socio-demographical data of mothers.Postpartum visit (7–10 days): Clinical data questionnaire – Newborn variables.Fortieth-day visit (4–6 weeks): Questionnaire on breastfeeding accessories and mother's nutrition variables.

All study variables are described in Annex II. Recruiting midwives are to be trained on how to complete the 24-h dietary recall and to be provided with a visual food atlas as support (Annex III) to help women record ration measurements.

### Study variables

#### Dependent variables (outcomes)

*The environmental impacts* – climate change, water consumption, and water scarcity (for definitions see Annex I) – of the three infant feeding types and maternal diet:

*CC (climate change)* will be assessed in kg CO2eq by the IPCC GWP 100 years calculations [30];*WC (water consumption)* will be calculated in m3 following the ReCiPE method [31], calculating direct and indirect water consumption.* WS (water scarcity)* will be calculated in m3eq using the AWARE method [32].

